**4.4 Eligibility Criteria**

- Patients diagnosed cancer
- Age 18 years or older, up to 70 years old
- Both sexes
- Classified as PS score 0 or 1
- Patients who are rated Zero Risk or Low Risk by the falls risk assessment scale
- Indication for elective surgery

**4.5 Non-eligibility criteria**

- Patients who, moments before surgery, present an adverse event that may jeopardize walking to the operating room.
- Patients who have a physical disability and need help to walk.
- Patients who have an indication for a bed in the Intensive Care Unit (ICU)
- Patients who have previously diagnosed psychiatric disorders (severe depression, anxiety disorder, panic, among others).
- ECOG patients > 1.
- Patients who do not have a companion on the day of surgery.
- Patients using anxiolytic and antidepressant medications.

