**4.3 Sample calculation**

Based on the results found by Kojima e*t al.* ([12](#_ENREF_12)) A sample size was calculated to compare proportions. Considering a α error of 0.05 and a power of 1 – β of 0.80, a sample size of 176 patients was reached, with 88 patients allocated to the stretcher group, and 88 patients allocated to the ambulation group.

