**4.6 Data Collection**

A research instrument will be made on the REDCap data platform. In it, we will collect socio-demographic data such as: date of admission, date of birth, weight, height, gender, ethnic group, current residence, contact telephone number, name of the companion and their degree of kinship, socioeconomic level, education. We will use the source document (medical record) for information such as: classification of malignant tumors (TNM), classification of performance status according to comorbidities, classification of the fall risk scale, which is performed at the time of the patient's hospitalization by the employee responsible for the same, medications in use, other surgeries, complementary exams confirming the presence of cancer, the type and location of the neoplasm, date of surgery, surgical size.

Patients will be identified as potential participants for the study at the time of their admission. Fulfilling all the eligibility criteria, it will be randomized randomly through the REDCap platform, and the orientation of which group the patient fell will be carried out, for the nursing professional (stretcher bearer) who will take him to the operating room.

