Group 1 will be welcomed in their room by a nursing technician, a family member and the stretcher bearer who will take them lying on a stretcher to the operating room, accompanied by their family member, where they will be received by a nursing professional who will perform the standard procedures of the operating room. Group 2 will leave their room and go to the operating room walking with a family member and the stretcher bearer who will accompany them during the journey. Patients randomized to group 1 should be taken to the operating room in hospital clothes, while patients randomized to group 2 should be taken to the operating room with their own clothes. Upon entering the operating room, both patients in groups 1 and 2 will answer the questionnaire HAD scale – assessment of the level of anxiety and depression, easy to handle and quickly executed, which was developed to detect states of anxiety and depression in physically ill patients, who can answer it alone ([13](#_ENREF_13), [14](#_ENREF_14)) (APPENDIX 1), and the Questionnaire for the Evaluation of Satisfaction with Health Care in Surgery (Sati-Cir) (APPENDIX 2)), a questionnaire developed for the present study in order to evaluate patient satisfaction with the care received at the hospital, and to evaluate satisfaction with the way the patient was conducted to the operating room. For this questionnaire, a pilot test will be carried out with 20 patients who will have their way of conducting the operating room randomized randomly via RedCap, in order to analyze the patients' understanding of the questions asked.

After the application of both questionnaires, the Informed Consent Form (ICF) of the study will be applied. The application of the ICF will be carried out after the transport and application of the questionnaires in the operating room, so that there is no bias of the participant in the way he will answer the questionnaires, so as not to induce him to believe that being taken to the operating room walking is more comfortable and causes more satisfaction.

Both questionnaires will be used to evaluate the findings regarding emotional changes, degree of anxiety and satisfaction experienced by the patient at that moment, the questionnaires are self-administered or can be applied to the patient by members of the Researcher Support Center, and a scientific initiation student of the present study.

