**5. ETHICAL ISSUES**

This project is ethically and methodologically in accordance with the Guidelines and Regulatory Standards for Research involving Human Beings (Resolution 466/12 of the National Health Council) and will be submitted to the Institutional Review Board (IRB) of the Barretos Cancer Hospital. Patients will sign an informed consent form to participate in the study (APPENDIX 3). Failure to sign the term will result in the patient's non-participation in the study, but will not interfere with the patient's treatment at the institution.

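### A fitness-to-walk exclusion judged moments before surgery can act after the allocation is known, and no analysis rule keeps those patients in

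*Combined protocol and SAP*

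**What the plan says.** Two criteria in section 4.5 can be judged only on the day of surgery: "Patients who, moments before surgery, present an adverse event that may jeopardize walking to the operating room" and "Patients who do not have a companion on the day of surgery". Neither names an arm or says who makes the judgement.

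Section 4.6 sets the order of events: "Patients will be identified as potential participants for the study at the time of their admission". The next sentence makes randomisation conditional: "Fulfilling all the eligibility criteria, it will be randomized randomly through the REDCap platform". It then has the group passed on before the journey: "the orientation of which group the patient fell will be carried out, for the nursing professional (stretcher bearer) who will take him to the operating". No day or event is given for the randomisation, and section 4.8 (randomisation) adds none.

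Later in section 4.6, group 1 travels in hospital clothes and group 2 in its own clothes. The questionnaires are completed on entering the operating room. Consent comes last: "The application of the ICF will be carried out after the transport and application of the questionnaires in the operating room". Section 5 adds: "Failure to sign the term will result in the patient's non-participation in the study".

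Section 4.9 compares the two groups with standard tests. It defines no analysis population and does not say how patients lost after randomisation are handled.

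**The concern.** An exclusion does no harm to a randomised comparison when it is applied before allocation, or equally and without knowledge of the arm. The plan secures neither for the walking criterion. The event may arise at the last moment, when the bearer has been told the group and the patient is dressed for it.

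The criterion also has uneven practical force. A doubt about walking must be settled at once for a patient about to walk, whereas a stretcher patient with the same symptom can simply be taken. If the rule were used more in the walking arm, and those removed were more anxious than average, walking would look calmer with no true effect. Anxiety is the primary objective, and section 5.2 anticipates a benefit from walking, so the error would run in the expected direction. Patients dropped without a record cannot be recovered at analysis.

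**Working it through.** **1. Order of events.**

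- Admission: identification (4.6).
- Unstated time: randomisation, once the criteria are met (4.6).
- Before departure: the bearer is told the group (4.6). The ward must know it too, because clothing differs by arm.
- Moments before surgery: the walking criterion (4.5).
- On entering the operating room: questionnaires, then consent (4.6).

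Even if randomisation waits for a check of the walking criterion, an event can still arise between disclosure and arrival. As written, section 4.5 makes that patient ineligible after allocation, and section 4.9 does not bring the patient back.

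**2. The plan's own figure.** Section 4.3 states: "Considering a α error of 0.05 and a power of 1 – β of 0.80, a sample size of 176 patients was reached". That is 2 × 88, for a comparison of proportions. The two proportions and the sidedness are not given, so 176 can be neither reproduced nor refuted. For example, 60% v 39% two-sided and 90% v 76% one-sided both give 88 per arm. For scale only, at 88 per arm, two-sided 5% and 80% power:

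- proportions: about 17 to 21 points detectable for control rates of 30% to 80%;
- a score: (1.960 + 0.842) × √(2/88) = 2.802 × 0.1508 = 0.42 SD.

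**3. Bias on a score.** Every input here is an assumption; the documents give none. A fraction e is removed from the walking arm and none from the stretcher arm. Those removed are δ SD more anxious than those kept. There is no true effect, and the SD is held at 1.

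Bias = e × δ. SE = √(1/88 + 1/[88(1 − e)]). Type I error = Φ(bias/SE − 1.96) + Φ(−bias/SE − 1.96).

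- e = 5%, δ = 1: bias 0.05; SE = √(1/88 + 1/83.6) = 0.153; ratio 0.327; type I error 6.2%.
- e = 10%, δ = 1: bias 0.10; SE = √(1/88 + 1/79.2) = 0.155; ratio 0.646; type I error 9.9%.
- e = 5% and 10%, δ = 0.5: type I error 5.3% and 6.2%.
- δ = 0: bias 0; type I error 5%.

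Against 0.42 SD, biases of 0.05 and 0.10 SD are 12% and 24%.

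**4. Bias on a proportion.** Assume 50% anxious in both arms, no true effect, and an anxiety rate q among those removed. The walking-arm rate becomes (0.50 − e × q)/(1 − e). The rejection probability is for a two-sided pooled z-test.

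| e | q | Walking-arm rate | Spurious difference | Type I error |
|---|---|---|---|---|
| 5% | 50% | 50.0% | 0 | 5.0% |
| 5% | 70% | 0.465/0.95 = 48.9% | 1.1 points | 5.2% |
| 5% | 100% | 0.450/0.95 = 47.4% | 2.6 points | 6.4% |
| 10% | 70% | 0.430/0.90 = 47.8% | 2.2 points | 5.9% |
| 10% | 100% | 0.400/0.90 = 44.4% | 5.6 points | 11.0% |

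The loss of numbers matters less. For an assumed 50% v 29.3%, power falls from 80.7% to 79.6% at e = 5% and to 78.4% at e = 10%.

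**The case against.** The strongest reply is that section 4.6 already makes randomisation conditional on all criteria. If the section 4.5 list counts among them, randomisation would follow the day-of-surgery checks, and what remains is a missing time. The criterion also names no arm. Applied equally, it narrows the population without biasing the comparison. Nothing shows that patients unwell just before surgery are more anxious, and a removal rate of 0% in the stretcher arm is the extreme case.

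Much of this stands, and it limits the point. A reader might infer that patients are randomised at admission, that staff who know the arm apply the exclusion, and that it falls mainly on the walking arm. The documents do not say so. Only identification is placed at admission, the bearer is told the group but is given no role in exclusions, and the criterion is worded for everyone.

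Two neighbouring points do not show arm-selective removal either:

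- **Companion.** This criterion shares the timing gap, but both arms travel with a family member, so a missing companion disqualifies equally.
- **Fall risk.** A score can go out of date: in Table 2, two or more medications (5) plus one device (1) make 6, Moderate Risk. But section 4.6 uses the classification made at hospitalisation and nothing says it is repeated. A score that is not re-applied removes nobody after randomisation.

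The reply does not close the route. The text does not require the late criteria to be checked before the group is disclosed, an event can arise after disclosure, and no rule covers a randomised patient who then meets the criterion.

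**Conclusion.** The concern holds as an open route to bias, not as a demonstrated one. The timing of randomisation relative to the walking criterion is undefined, the criterion can act once the group is known, and section 4.9 does not keep such patients in. Greater removal from the walking arm is plausible, not documented.

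The size is unknown. It ranges from nil, if those removed are no more anxious than the rest, to a type I error of about 6–10% under the assumed 5–10% one-sided removal and 1 SD gap. A milder gap leaves the error close to 5%. A reader might conclude that the randomised comparison is lost; that goes further than the documents allow. The one loss after randomisation that the plan does build in is refusal of the late consent, and it is not accounted for by arm either. Because the remedy is cheap and the patients cannot be recovered later, the change is worth making.

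**What to change.** **Section 4.6.** Randomise on the day of surgery, as late as practical before dressing and transport. Do so after all section 4.4 and 4.5 criteria have been confirmed in every patient, and before the group is disclosed to anyone. Word the section 4.5 walking criterion so that it is judged at that check.

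**Section 4.9.** Analyse every randomised patient who gives consent in the allocated arm. Treat a later event or a change of transport as a recorded deviation with the questionnaires still collected, not as an exclusion. Report all losses after randomisation by arm and reason, including refusal of consent and any patient who never reaches the questionnaires. The restriction to consenting patients is needed because consent follows the questionnaires and refusal means non-participation.

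How an unwell patient travels stays with the clinical team; these changes concern only who is counted and in which arm.

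**Cost.** A change in the timing of the REDCap step and a few sentences in sections 4.5, 4.6 and 4.9. The ward and the bearer get the allocation later, which could slightly delay dressing and transfer.

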**4.6 Data Collection**

A research instrument will be made on the REDCap data platform. In it, we will collect socio-demographic data such as: date of admission, date of birth, weight, height, gender, ethnic group, current residence, contact telephone number, name of the companion and their degree of kinship, socioeconomic level, education. We will use the source document (medical record) for information such as: classification of malignant tumors (TNM), classification of performance status according to comorbidities, classification of the fall risk scale, which is performed at the time of the patient's hospitalization by the employee responsible for the same, medications in use, other surgeries, complementary exams confirming the presence of cancer, the type and location of the neoplasm, date of surgery, surgical size.

Patients will be identified as potential participants for the study at the time of their admission. Fulfilling all the eligibility criteria, it will be randomized randomly through the REDCap platform, and the orientation of which group the patient fell will be carried out, for the nursing professional (stretcher bearer) who will take him to the operating room.

Group 1 will be welcomed in their room by a nursing technician, a family member and the stretcher bearer who will take them lying on a stretcher to the operating room, accompanied by their family member, where they will be received by a nursing professional who will perform the standard procedures of the operating room. Group 2 will leave their room and go to the operating room walking with a family member and the stretcher bearer who will accompany them during the journey. Patients randomized to group 1 should be taken to the operating room in hospital clothes, while patients randomized to group 2 should be taken to the operating room with their own clothes. Upon entering the operating room, both patients in groups 1 and 2 will answer the questionnaire HAD scale – assessment of the level of anxiety and depression, easy to handle and quickly executed, which was developed to detect states of anxiety and depression in physically ill patients, who can answer it alone ([13](#_ENREF_13), [14](#_ENREF_14)) (APPENDIX 1), and the Questionnaire for the Evaluation of Satisfaction with Health Care in Surgery (Sati-Cir) (APPENDIX 2)), a questionnaire developed for the present study in order to evaluate patient satisfaction with the care received at the hospital, and to evaluate satisfaction with the way the patient was conducted to the operating room. For this questionnaire, a pilot test will be carried out with 20 patients who will have their way of conducting the operating room randomized randomly via RedCap, in order to analyze the patients' understanding of the questions asked.

After the application of both questionnaires, the Informed Consent Form (ICF) of the study will be applied. The application of the ICF will be carried out after the transport and application of the questionnaires in the operating room, so that there is no bias of the participant in the way he will answer the questionnaires, so as not to induce him to believe that being taken to the operating room walking is more comfortable and causes more satisfaction.

Both questionnaires will be used to evaluate the findings regarding emotional changes, degree of anxiety and satisfaction experienced by the patient at that moment, the questionnaires are self-administered or can be applied to the patient by members of the Researcher Support Center, and a scientific initiation student of the present study.

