Cancer patients present emotional changes from the moment of their diagnosis and throughout the treatment, for this reason, the study wants to observe if there is any change in the emotional responses, the degree of anxiety and the satisfaction of adult cancer patients classified as PS 0 and 1 according to the change in the type of transport to the operating room, replacing the use of stretchers (traditional model) with ambulation. In addition, there is a deficit of studies published in the literature on this topic, especially in cancer patients, and according to the final findings, it can change the daily practice in relation to the way these patients are taken to the operating room, reducing anxiety levels and thus resulting in a better recovery of the patient.

- 1. **Factor under Study**

Way of driving to the operating room (stretcher versus ambulation)

- 1. **Primary outcome**

Emotional impact according to the way they were driven to the operating room.

1. **OBJECTIVES**
   1. **Primary objective**

**3.1.1** Determine the anxiety levels of the patient diagnosed with cancer according to the type of transport to the operating room.**.**

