**Part A**

|  | Very Satisfied | Satisfied | Indifferent | Dissatisfied | Very Dissatisfied |  |  |  |  |  |
| --- | --- | --- | --- | --- | --- | --- | --- | --- | --- | --- |
| 1. *How satisfied are you with clarifying doubts about your illness?* | 1 | 2 | 3 | 4 | 5 |  |  |  |  |  |
| 1. *How satisfied are you with your participation in decisions related to your treatment?* | 1 | 2 | 3 | 4 | 5 |  |  |  |  |  |
| 1. *How satisfied are you with the opportunities the team gives you to ask questions?* | 1 | 2 | 3 | 4 | 5 |  |  |  |  |  |
| 1. *How satisfied are you with the way you get information when you ask for it?* | 1 | 2 | 3 | 4 | 5 |  |  |  |  |  |
| 1. *How satisfied are you with the care provided by the nursing team to preserve your privacy?* | 1 | 2 | 3 | 4 | 5 |  |  |  |  |  |
| 1. *How satisfied are you with the time you waited until you were admitted?* | 1 | 2 | 3 | 4 | 5 |  |  |  |  |  |
| 1. *How satisfied are you with the time you waited until the surgery?* 2. *How were you taken to the surgical center:* | 1 | 2  stretcher bearer | 3 | 4  walking | 5 |  |  |  |  |  |
| 1. *How satisfied are you with the way you were taken to the surgical center?* 2. *How were you taken to the surgical center:* | 1 | 2  Pajama | 3 | 4  their own clothes | 5 | 1 | 2 | 3 | 4 | 5 |
| 1. *How satisfied are you with the clothing you wore when taken to the surgical center?* | 1 | 2 | 3 | 4 | 5 |  |  |  |  |  |

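### Clothing is assigned together with transport, so a difference between the arms cannot be attributed to walking alone

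*Combined protocol and SAP*

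**What the plan says.** The Justification names a single factor under study: "Way of driving to the operating room (stretcher versus ambulation". The primary objective (3.1.1) is "Determine the anxiety levels of the patient diagnosed with cancer according to the type of transport to the operating room". The four secondary objectives (3.2.1 to 3.2.4) are framed by transport in the same way, for depression, satisfaction, and anxiety by gender and by socioeconomic level. Section 4.8 defines the two arms by transport and adds only that both are accompanied by family. Section 4.9 plans simple two-group tests, with the groups labelled by transport.

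Section 4.6 adds a second instruction by arm: group 1 goes "to the operating room in hospital clothes, while patients randomized to group 2 should be taken to the operating room with their own clothes". No section explains this difference, presents the intervention as a combination, or lists clothing as a limitation.

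The Sati-Cir questionnaire (Appendix 2) treats clothing as worth asking about in its own right. Part A includes "How satisfied are you with the clothing you wore when taken to the surgical center", alongside a separate item on how the patient was conducted. Part B asks whether dignity and privacy were preserved with respect to the clothing.

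On staff, section 4.6 says "Group 1 will be welcomed in their room by a nursing technician, a family member and the stretcher bearer", and for the other arm "Group 2 will leave their room and go to the operating room walking with a family member and the stretcher bearer".

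**The concern.** Randomisation makes the two groups comparable at baseline. It does not separate two things that are always given together. Here every stretcher patient is to wear hospital clothes and every walking patient their own.

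The mechanism the protocol proposes for walking could plausibly operate through clothing too. The Introduction reports that stretcher patients feel inferior and conspicuous, and section 5.2 hopes that walking will weaken the sense of being ill and incapable. Being in one's own clothes might act in the same direction.

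What is at stake is the conclusion. The Justification and section 5.2 both say the findings may change how patients are taken to the operating room. If clothing contributed to a favourable result, a transport-only conclusion would credit walking with an effect that is partly or wholly not its own. If clothing worked against walking, a real transport effect could be hidden.

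**Working it through.** This is a question of what the design can identify, so the check is on the design and not on a stated figure.

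**Inputs.** The arms and the clothing by arm come from sections 4.6 and 4.8. The planned tests come from section 4.9. The sample size (88 + 88 = 176) comes from section 4.3.

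**Step 1: combinations randomised.** Let T = 1 for walking and 0 for stretcher, and C = 1 for own clothes and 0 for hospital clothes.

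| Arm | T | C |
| --- | --- | --- |
| Group 1 | 0 | 0 |
| Group 2 | 1 | 1 |

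The cells (T = 1, C = 0) and (T = 0, C = 1) do not occur under the plan.

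**Step 2: what is estimable.** Write the mean outcome as μ + τT + κC. The group 1 mean is μ and the group 2 mean is μ + τ + κ. Their difference is δ = τ + κ. The design matrix has rows (1, 0, 0) and (1, 1, 1), hence rank 2 for three parameters. Only μ and the sum τ + κ can be estimated. An interaction between walking and clothing, if there is one, is absorbed into the same sum.

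**Step 3: whether analysis or size helps.** Adding patients repeats the same two rows and leaves the rank at 2. Because C equals T for every patient, a clothing covariate is a copy of the treatment indicator. The t-test, Mann-Whitney, chi-square and Fisher tests in section 4.9 all address δ.

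**Step 4: whether the share can be bounded.** For any observed δ, τ = δ − κ for any value of κ. The pairs (τ, κ) = (δ, 0), (0, δ) and (−δ, 2δ) all give the same data, with clothing shares κ/δ of 0, 1 and 2. The share is therefore not confined to 0–100%, and the documents give nothing from which to estimate it.

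**Step 5: whether the questionnaire rescues it.** The Sati-Cir items on transport and on clothing are separate questions, but each is answered by patients who received both exposures together. The HADS (Appendix 1), used for anxiety and depression, has no such split.

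**Step 6: sample size under identical clothing.** The comparison remains 88 versus 88, so power for any given difference is unchanged. Section 4.3 does not state the two proportions, so 176 can be neither reproduced nor faulted. Assuming a two-sided test without continuity correction, 88 per arm at 80% power fits differences from about 9 points (10% versus 0.6%) to 21 points (60% versus 39%), depending on the unknown control rate. The point does not depend on these figures.

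**Step 7: the nursing technician.** Section 4.6 names a technician in the group 1 welcome and says nothing either way for group 2. The travelling party is the same in both arms: stretcher bearer and family member. If the welcome did differ, there would be four parameters on rank 2, and the conclusion on attribution would be the same.

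**The case against.** The strongest reply is that this is a pragmatic comparison of the hospital's traditional procedure with a new one. Bundled interventions are legitimate, and the practical aim is to decide how patients should be conducted. The Sati-Cir layout lends this some support: in Part A, as far as the broken table can be read, the question on how the patient was taken appears with clothing options as well as transport options. It is also fair that the clothing items concern satisfaction and dignity, that no section says clothing affects HADS anxiety, and that the Introduction attributes distress on a stretcher to lying down and drawing attention.

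Much of this stands. The comparison of the two procedures as delivered is randomised and valid. What does not stand is the label: the factor, objectives, arms and analysis are all written for transport alone, and no section describes a package or says that walking requires own clothes.

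Three stronger readings are tempting, and the documents do not support them:

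- **The trial answers nothing.** It answers whether the two procedures differ.
- **A benefit would really be a clothing effect.** That is a logical possibility whose size the documents do not indicate.
- **Only the stretcher arm receives a nursing technician.** Section 4.6 is silent for group 2, which is not a statement of absence. The same group 1 sentence is also the only one to mention standard reception by operating-room nursing staff, which is hard to read as withheld from group 2. Uneven description is the likelier explanation.

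**Conclusion.** The point holds for clothing. As written, the plan would support a valid conclusion about walking in own clothes versus lying on a stretcher in hospital clothes, but not a conclusion about transport alone. The aliasing is complete: one estimable contrast for two effects. The clothing share of any difference in anxiety, depression or satisfaction is unknown and not identifiable, so no percentage should be attached to it.

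This rests on section 4.6 being followed as written. It does not rest on any assumption about the size or direction of a clothing effect, nor on the sample size. The technician's welcome is a matter for clarification and not an established difference between the arms.

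**What to change.** Which remedy is open depends on recruitment status. The document is dated 2020, and section 7 schedules data collection across 2019 and 2020, but it does not say how many patients have been enrolled.

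- **If recruitment has not begun, or the change can be handled without mixing two interventions:** specify in section 4.6 the same clothing in both arms. This costs one procedural sentence and a ward instruction, with 88 per arm unchanged. The small downside is that the combined package is no longer tested. The stated 80% power carries over only if the difference assumed in section 4.3 is meant for transport alone. This change cannot repair data from patients already enrolled.
- **Otherwise:** reword the factor under study, objectives 3.1.1 and 3.2.1 to 3.2.4, the group labels in section 4.9 and the planned conclusion as *walking in own clothes versus stretcher in hospital clothes*, and state that no claim will be made about transport alone. This costs a few sentences and no patients, but gives up the transport-only claim.

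In either case, add a sentence to section 4.6 saying whether the nursing technician's welcome also applies to group 2.

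### Staff who can see the arm may apply the anxiety questionnaire, with no rule for when and no record of mode or interviewer, so interviewer or mode effects could mimic or mask a transport effect

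*Combined protocol and SAP*

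**What the plan says.** The primary objective (3.1.1) is to "Determine the anxiety levels of the patient diagnosed with cancer according to the type of transport to the operating room". Anxiety is measured with the HADS, a subjective patient report, which 4.6 describes as "developed to detect states of anxiety and depression in physically ill patients, who can answer it alone".

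On timing, 4.6 says: "Upon entering the operating room, both patients in groups 1 and 2 will answer the questionnaire HAD scale". The satisfaction questionnaire (Sati-Cir) is given at the same sitting. On mode, 4.6 says that "the questionnaires are self-administered or can be applied to the patient by members of the Researcher Support Center, and a scientific initiation student" may administer them, and it identifies the student as belonging to this study.

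The arms look different on arrival. Group 1 comes with "the stretcher bearer who will take them lying on a stretcher to the operating room, accompanied by their family member", while group 2 walks in. On clothing, "Patients randomized to group 1 should be taken to the operating room in hospital clothes", while group 2 wears its own. Sati-Cir Part A also asks: "How were you taken to the surgical center".

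The only precaution against response bias in 4.6 is that consent is sought after the questionnaires. Its stated purpose is to keep the participant from being led. The data items listed in 4.6 do not include mode or interviewer. Section 4.9 plans a t-test or Mann-Whitney test, or a chi-square or Fisher test, with no adjustment.

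**The concern.** Answers about anxiety and satisfaction given aloud to hospital or study staff can differ from answers written in private. Someone who knows both the arm and the hypothesis can also influence replies through tone, prompting or interpretation. The protocol states the direction it hopes for: the Introduction reports that walking patients were calmer in an earlier study, and 5.2 anticipates a psychological benefit. Delayed consent protects against expectation in the patient, but nothing comparable protects against expectation in the person asking.

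There are two routes to bias. The first is interviewing by someone who knows the arm, which can bias the comparison even when equal shares of both arms are interviewed. The second is a mode split that differs by arm, so that a mode effect is counted as a transport effect. Neither route has a known direction: the result could be a spurious difference or a hidden real one. Because mode and interviewer are not recorded, neither could be examined afterwards.

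**Working it through.** **The plan's own figure.** Section 4.3 gives 176 patients (88 per arm) for comparing proportions, at alpha 0.05 and power 0.80. It states neither proportion, so the figure can be neither confirmed nor refuted. Many pairs give 88 per arm with a two-sided test and no continuity correction, for example 0.60 vs 0.39 or 0.85 vs 0.67. Only the 88 per arm is used below.

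**Inputs.** From the documents: 88 per arm and alpha 0.05 (taken as two-sided, since sidedness is not stated). Assumed, because the documents give no value: the mode effect *m* in SD units, the gap *g* between arms in the share interviewed, and a common SD of 1.

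**Formulas, with no true transport effect.**
- Bias from mode: *b* = *m* × *g*. If *g* = 0, then *b* = 0.
- Standard error of the difference: √(2/88) = 0.151 SD.
- Rejection rate: 1 − Φ(1.96 − *b*/0.151) + Φ(−1.96 − *b*/0.151).
- Detectable difference at 80% power: (1.960 + 0.842) × 0.151 = 0.42 SD.

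| Mode effect *m* (SD) | Gap *g* (points) | Bias *b* (SD) | False-positive rate |
|---|---|---|---|
| any | 0 | 0 | 5.0% |
| 0.2 | 20 | 0.04 | 5.8% |
| 0.2 | 40 | 0.08 | 8.3% |
| 0.3 | 20 | 0.06 | 6.8% |
| 0.3 | 40 | 0.12 | 12.5% |
| 0.5 | 20 | 0.10 | 10.2% |
| 0.5 | 40 | 0.20 | 26.4% |

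**On the score scale.** Suppose 70% of stretcher and 30% of walking patients are interviewed, interview shifts the anxiety score by 1 point, and the SD is 4 (all assumed). The bias is (0.70 − 0.30) × 1 = 0.40 points. That is 0.40/4 = 0.10 SD, with a false-positive rate of about 10%. The detectable difference is 0.42 × 4 ≈ 1.7 points, so the bias is about 24% of it.

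**If anxiety is analysed as a proportion** (the basis of 4.3): at an assumed 50% in both arms, a 20-point mode effect with a 40-point gap gives 0.20 × 0.40 = 8 points of bias. The false-positive rate is then 18.6%.

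**Interviewer influence with balanced mode.** If staff who know the arm shift the difference between arms by 0.1 or 0.2 SD (assumed), the rejection rate is 10.2% or 26.4%.

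**The case against.** The wording in 4.6 can be read as self-completion by default with staff as a fallback, especially as the HADS is described as something patients can answer unaided. That is a fair reading. On it, the gap is a fallback that has no criterion and is not recorded, which still leaves the problem.

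A reader might infer that stretcher patients will be interviewed more often because they arrive lying down. The documents do not support this. They describe the position during transport and do not say that patients answer lying down. All patients are ECOG 0 or 1, at zero or low fall risk, and able to walk unaided (4.4, 4.5). Randomisation should balance literacy and eyesight on average. An arm difference in mode is therefore a possibility only, and without one, mode by itself adds noise and no bias.

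A reader might also infer that the bias would favour walking. Nothing in the documents fixes its direction.

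The sizes above rest on assumptions throughout, and at the mild end the effect is small (5.8% against 5%). The Sati-Cir item that reveals the arm adds little, since arrival and clothing already show it and 4.6 names the HADS first.

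What stands is that study staff who can see the arm are permitted to apply a subjective primary outcome, with no rule for when and no record of it.

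**Conclusion.** The point holds in limited form. As written, 4.6 leaves HADS anxiety and Sati-Cir open to influence from an interviewer who knows the arm and to an unrecorded mode imbalance, and 4.9 could neither detect nor correct either one. The effect could mimic or mask a transport effect.

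Its size is unknown. Across the assumed range (0.2 to 0.5 SD mode effect, 20 to 40 point gap, 88 per arm, no true effect), the bias is 0.04 to 0.20 SD, against a detectable 0.42 SD. The false-positive rate is about 6% to 26%. The documents do not show that the modes will differ by arm or that any result will be wrong. The reason to act is that a better procedure costs little and fits the plan's own description of the HADS.

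**What to change.** **In 4.6.** State that all patients in both arms self-complete both questionnaires at the same point after arrival, HADS first. Allow verbatim reading aloud only for patients who cannot read, see or write on the form, on the same criterion in both arms, and not by the study student. Record mode and reader in REDCap.

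**In 4.9.** Report mode by arm. Add a sensitivity analysis on self-completed forms, labelled as supportive: it selects on a post-randomisation feature, so it does not replace the main analysis.

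**If forms are already collected.** The document is dated 2020, and the schedule in section 7 places data collection in 2019 and 2020. In that case, recover the mode where possible, report it by arm and state the limitation.

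**Cost.** Short edits to 4.6 and 4.9, one or two REDCap fields, and slightly longer completion for some patients. A reader may still see the arm, so the change reduces interviewer influence without fully removing it.
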